### Data analysis

The main objectives of Project STARLIT are to characterize trajectories of habitual sleep across the four time points, determine whether sleep trajectories are related to weight gain risk behaviors, and identify what factors may contribute to sleep trajectory group membership. In order to characterize the sleep trajectory groups, we will use finite mixture models adapted for the case where the analysis focuses on trajectories [43–49]. The conceptual underpinning of this model is that each participant is a member of one of an unknown number of latent classes with a unique “trajectory type”, and their class membership determines their mean trajectory. The primary analytic goals of that analysis are to determine both the number of trajectory groups, and their characteristics. To determine the number of classes, several plausible fixed numbers of groups will be examined and the number of trajectories that optimizes a given information-based model selection criterion will be used [46, 47, 49]; diagnostics based class separation (e.g., using relative entropy) will also be used to evaluate the model fit. While the hypothesized variable of interest is sleep duration, the data will be examined to determine if another variable may be a better representation of the pattern of data (e.g., mean difference between weekday and weekend sleep time, or the % of days under 6 h). If that is the case, separate analyses will be conducted for each variable of interest.

To determine whether sleep trajectories are related to weight gain risk behaviors, each individual will be assigned to a latent class (i.e., trajectory type) based on the maximum posterior probability, and the latent class label will be used as a categorical predictor in a series of ANOVA/regression models predicting the various weight gain risk outcomes (i.e., increased caloric intake, decreased physical activity, weight gain, and increased body fat composition). Lastly, using multinomial logistic regression models, the identification of what factors contribute to latent glass group membership will be examined. Specifically, the assigned latent class variable will be used as the outcome variable and baseline measures of sleep-risk as predictors (i.e., amount of media and technology usage, problematic sleep-related beliefs/behaviors).

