This paper describes the protocol of Project STARLIT, which is a two-year prospective longitudinal study examining the relationship between habitual sleep and weight gain, along with obesity risk behaviors in a sample of Freshmen college students recruited during new student orientation. There appears to be a critical period in which habitual sleep changes have a maximum impact on weight gain [29]; therefore, recruiting recent high school graduates prior to the start of college may be an opportune time to observe the onset or exacerbation of habitual short sleep. The primary hypothesis is that we will observe different habitual sleep trajectories over time. The secondary hypothesis is that two sleep trajectories (stable habitual short sleep and increasingly shorter habitual sleep across time) will be significantly related to weight gain, increased body fat percent, and weight gain risk behaviors (i.e., increased average daily caloric intake and less daily average time spent engaging in moderate- and vigorous-intensity physical activities). We are not aware of any other studies that have attempted to relate sleep trajectories to behaviors most indicative of weight gain and obesity risk. This study will use objective measures of sleep, physical activity, and body fat composition as well as a gold standard measure of caloric intake; objective measurement is important because previous longitudinal investigations have primarily used self-report measures of sleep and physical activity, which can provide inaccurate information [23]. The supplemental hypothesis is that the two sleep trajectories (stable habitual short sleep and increasingly shorter habitual sleep across time) will be significantly associated with higher rates of media and technology use and higher rates of problematic sleep-related beliefs/behaviors (e.g., sleep difficulties, delayed sleep scheduling, sleep fragmentation, sleep hygiene problems, alcohol and caffeine usage, dysfunctional beliefs, napping).

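### The sleep variable behind the trajectories can be added to after the data are examined, and the plan does not say that duration stays the confirmatory version

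*Protocol article*

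**What the plan says.** All of the operative text is in the protocol article.

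- **Trajectory variable (Data analysis).** The sentence begins "While the hypothesized variable of interest is sleep duration" and goes on to say that "the data will be examined to determine if another variable may be a better representation of the pattern of data". Two candidates are offered as examples: "e.g., mean difference between weekday and weekend sleep time, or the % of days under 6 h". The consequence follows: "If that is the case, separate analyses will be conducted for each variable of interest".
- **Use of the classes (Data analysis, next paragraph).** Each participant is assigned to the most probable class, and "the latent class label will be used as a categorical predictor in a series of ANOVA/regression models". The outcomes are listed as "i.e., increased caloric intake, decreased physical activity, weight gain, and increased body fat composition".
- **Secondary hypothesis (Background).** Two trajectories, one of persistently short sleep and one of sleep that shortens over time, "will be significantly related to weight gain, increased body fat percent, and weight gain risk behaviors". The same section defines habitual short sleep as a nightly average below 6 hours.

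The article gives no criterion for what makes a variable better and no point in time by which the choice must be made. It does not separate the choice from the outcome data, and it does not label the additional analyses.

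**The concern.** The secondary hypothesis predicts significant relations for two trajectories that are both defined by how long people sleep. The plan then allows the sleep data to be inspected, further sleep variables to be taken from an open list, and a separate analysis to be run for each. Three problems follow.

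1. Each trajectory solution yields its own class label, and that label is the predictor in the outcome models. One hypothesis could therefore be tested on several exposures, with no version marked in advance as the one that counts.
2. Some candidates do not measure the thing hypothesised. A person can have a large weekday-weekend difference with long or with short average sleep.
3. A reader of the results could not tell whether a significant association came from the exposure the study set out to test or from one adopted later.

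The Discussion proposes to develop sleep interventions if the hypotheses are supported, so it matters which analysis counts as support.

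**Working it through.** **Inputs**

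- Sleep variables: 1 hypothesised (duration) plus 2 named as examples, so 3 (Data analysis). The list is open, so 3 is not a ceiling.
- Outcomes: 4, namely caloric intake, physical activity, weight and body fat (Data analysis).
- Tests per outcome: 1, because the class label enters as one categorical predictor. This is read from the wording of the model.
- Level per test: 5%. This is an assumption; the article states no significance level.
- Participants analysed: 300 × (1 − 0.20) = 240, which reproduces the figure under Sample size justification. It is used only in the simulation below. The article gives no error rate that could be reproduced.

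**Chance of at least one false positive, m independent tests:** 1 − (1 − 0.05)^m

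| Sleep variables | m | Calculation | Result |
|---|---|---|---|
| 1 | 1 × 4 = 4 | 1 − 0.95^4 = 1 − 0.8145 | 18.5% |
| 2 | 2 × 4 = 8 | 1 − 0.95^8 = 1 − 0.6634 | 33.7% |
| 3 | 3 × 4 = 12 | 1 − 0.95^12 = 1 − 0.5404 | 46.0% |

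The 12-test figure covers any result that might be presented as support. If weekday-weekend classes are left out because they do not test the hypothesis, the 8-test row applies.

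**Effect of correlation.** A simulation with no true effects used 4,000 runs per setting, 240 participants, four equal classes and a one-way ANOVA for each outcome. Assumed correlations ran from 0 to 0.6 between outcomes and from 0 to 0.8 between sleep variables.

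- 4 tests on duration alone: 14.2% to 18.9%.
- 4 tests on one variable substituted without regard to the outcomes: 14.4% to 18.7%, the same level as duration alone.
- 12 tests on three variables: 34.6% to 45.2%.

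Substitution made blind to the outcomes therefore adds nothing. The extra error comes from running several versions, or from choosing among them after the outcomes are seen.

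**Fit to the hypothesis**

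- Mean sleep duration: measures sleep length, and matches the Background definition of short sleep.
- Percentage of days under 6 hours: related to short sleep, but a frequency below a cut-off rather than an average.
- Weekday-weekend difference: measures irregularity, so a class of short or shortening sleep is undefined for it.

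**The case against.** The strongest reply is that the clause is milder than it looks. It stands in the paragraph on the sleep mixture model, ahead of any outcome model, and its stated criterion is how well a variable represents the sleep pattern. On that reading the choice rests on sleep data alone, and the simulation confirms that such a choice does not by itself raise the error rate. The stated consequence adds analyses and does not displace duration, which remains the named hypothesised variable. The article also condenses a fuller document, and the study is observational and uses a method it calls relatively novel.

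Much of this stands, and it rules out several stronger readings that a reader might infer:

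- *That analysts will pick whichever exposure gives significance.* The text does not describe this. It only fails to exclude it.
- *That every outcome test is stated to be rerun for each variable.* This is the natural consequence of how the class label is used, but the article does not spell it out.
- *That the two risk classes should be counted separately, giving 8 and 24 tests and error rates of about 34% and 71%.* The class label is one categorical predictor, so one test per outcome is the better count.
- *That all the study's hypotheses lose error control.* The primary hypothesis, that distinct trajectories exist, is settled by an information criterion and class-separation diagnostics, without p-values.
- *That the lack of a multiplicity adjustment across the four outcomes is itself the defect.* That is commonly left to an analysis plan, which is not shown here.

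What the reply does not remove is the rule itself. The article affirmatively sets out a data-dependent step with an open list and repeated analyses, and it does not say which version carries the secondary hypothesis. That is a choice fixed badly, and goes beyond omitted detail.

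**Conclusion.** The concern holds for the secondary hypothesis. As written, the plan permits that hypothesis to be examined on several sleep variables, at least one of which does not measure sleep length, with none reserved as confirmatory and no requirement that the choice precede sight of the outcomes. Using all three named variables would take the chance of at least one false positive from 18.5% to 46.0%, or from 14–19% to 35–45% across the correlations simulated. These figures are illustrations. They depend on the assumed 5% level, on one omnibus test per outcome, and on the inference that the outcome models are repeated for each set of classes. The difference between the two figures is what this clause can add; the 18.5% arises from having four outcomes and would be there without it. The point is worth correcting, but it does not undermine the trajectory analysis.

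**What to change.** In Data analysis, state that:

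1. actigraphic mean sleep duration is the only trajectory variable for the confirmatory test of the secondary hypothesis, fixed before sleep data are linked to any outcome;
2. the alternatives form a closed list (for example, the two already named), are labelled exploratory, and are reported whatever they show.

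This takes a few sentences and no extra data, and every alternative analysis the authors want can still be run. The price is that the alternative measures can no longer carry a confirmatory claim, even if one proves to describe the sleep data better.

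Fixing the variable reduces the family from 12 tests to 4 but does not bring the overall rate to 5%. Control across the four outcomes may be left to the analysis plan. For scale, a Bonferroni level would be 0.05/4 = 0.0125 with duration alone, against 0.05/12 = 0.0042 if all three variables kept equal standing.

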### Sample size justification

The examination of sleep trajectories is a relatively novel approach and the power to detect differences among trajectory types is dependent on multiple factors [50]. Therefore, sample size is difficult to estimate prospectively with certainty for two reasons, 1) the size and separation of sleep trajectory types in our proposed sample is relatively unknown and 2) the size and separation of trajectory types is one of the most important factors for determining the power necessary to detect trajectory types. However, with a sample size of *N* = 200, trajectories with a medium and high level of heterogeneity (i.e, among slopes and/or intercepts) can be reliably detected; power > 80% and power > 95% [51]. Further, a brief simulation was conducted based on published sleep quality trajectories (albeit in a sample with different demographic characteristics) [52] and sleep quantity characteristics of young adults [i.e., setting a conservative with-in group standard deviation to 30 min [53];. With an estimated sample size of *N* = 300 (accounting for 20% attrition, *n* = 240) the model was able to recover the four sleep trajectories of previous research with a small level of variability.

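### Assigned trajectory class is analysed as if known without error, so class contrasts and odds ratios are biased, usually toward zero, to the extent that classification is imperfect

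*Protocol article*

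**What the plan says.** The Data analysis section of the protocol article sets out a classify-then-analyse sequence.

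- Assignment: "each individual will be assigned to a latent class (i.e., trajectory type) based on the maximum posterior probability".
- Class as predictor of weight, body fat, calorie and activity outcomes: "the latent class label will be used as a categorical predictor in a series of ANOVA/regression models".
- Class as outcome: "the assigned latent class variable will be used as the outcome variable and baseline measures of sleep-risk as predictors".
- Separation is examined only when the mixture model is judged: "diagnostics based class separation (e.g., using relative entropy) will also be used to evaluate the model fit".

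The Sample size justification section concedes that "the size and separation of sleep trajectory types in our proposed sample is relatively unknown". It describes a planning simulation, "setting a conservative with-in group standard deviation to 30 min", with 300 enrolled "accounting for 20% attrition", in which "the model was able to recover the four sleep trajectories of previous research with a small level of variability".

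The article mentions no posterior weighting, misclassification correction, joint model or entropy threshold that would alter the second stage. The analysis plan is not shown, but this is a rule the article states, not a detail it leaves out.

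**The concern.** A modal label is an estimate. Some participants placed in one class belong to another, so each assigned group is a mixture of true classes and its mean outcome is a weighted average of theirs. ANOVA and multinomial models that take the label as observed estimate contrasts between these mixtures, not between the trajectory types.

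The secondary hypothesis rests on two classes: stable short sleep and progressively shorter sleep. A declining class starts near a longer-sleeping class and ends near the short one, so with four visits it is a plausible candidate for confusion with both. The supplemental question, which baseline factors go with class membership, uses the same label as its outcome.

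If separation is only moderate, real associations with weight, body fat, intake and activity would be understated and power lost. The planning simulation does not settle this: recovering the mean curves of four classes does not show that individuals are classified correctly.

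**Working it through.** **Plan's own figure.** 300 × (1 − 0.20) = 240, as stated. The quoted power at N = 200 and the recovery simulation cannot be recomputed, because the article gives no class means or shares. The point does not depend on them.

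**Inputs from the article:** modal assignment, four visits, four classes in the planning simulation, within-group SD 30 min, n = 240. **Assumed, not in the article:** class means, class shares, within-class correlation ρ, outcome differences, and any SD other than 30 min.

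**Check 1: size of the bias with mixture parameters known (400,000 draws).** Classes: stable 8 h (35%), stable 7 h (35%), stable 5.75 h (15%), 7 falling to 5.75 h (15%). Mean outcomes are 0, 0, 1, 1 in that order.

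- Posterior: p(k | y) ∝ π_k φ(y; μ_k, Σ); the label is the k with the largest p.
- Mean in assigned class k: Σ_c P(true c | assigned k) × m_c.
- Fraction kept = contrast between assigned classes ÷ contrast between true classes.
- Relative entropy = 1 + ΣΣ p ln p ÷ (N ln 4).

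| SD (min) | ρ | Entropy | Declining vs 7 h | Short vs 7 h | Short vs 8 h |
|---|---|---|---|---|---|
| 30 | 0 | 0.89 | 0.88 | 0.95 | 1.00 |
| 30 | 0.5 | 0.76 | 0.85 | 0.86 | 0.93 |
| 45 | 0 | 0.69 | 0.70 | 0.84 | 0.96 |
| 45 | 0.5 | 0.52 | 0.64 | 0.66 | 0.83 |
| 60 | 0 | 0.53 | 0.57 | 0.71 | 0.90 |
| 60 | 0.5 | 0.37 | 0.49 | 0.53 | 0.74 |

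With mean outcomes 0, 0, 0.5, 1 instead and ρ = 0, short vs 8 h becomes 1.05, 1.10 and 1.08 at SD 30, 45 and 60. That contrast is inflated.

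**Check 2: full procedure at n = 240, SD 30 min.** The mixture was fitted by EM with the number of classes known and true starting values, which favours the plan. Assumed classes: adequate, stable short, declining and improving, with shares 40/25/20/15%. The true difference from adequate is 0.50 SD for stable short and for declining, and 0 for improving; 400 replicates. Results are given as stable short / declining.

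| Gap, ρ | Entropy | Misclassified | Modal estimate | Coverage |
|---|---|---|---|---|
| 120 min, 0 or 0.5 | 0.97-0.98 | 1-2% | 0.49-0.50 / 0.48-0.49 | 95-96% |
| 90 min, 0 or 0.5 | 0.87-0.90 | 6-7% | 0.45-0.49 / 0.46 | 93-95% |
| 60 min, 0.5 | 0.64 | 24% | 0.34 / 0.38 | 85% / 91% |
| 45 min, 0.5 | 0.52 | 40% | 0.29 / 0.29 | 78% / 82% |

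At gap 60, ρ = 0.5, power is 53% / 53%, against 86% / 80% if true class were observed.

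**Why coverage falls.** At gap 60, ρ = 0.5, stable short: model SE 0.171, sampling SD 0.168, bias 0.500 − 0.343 = 0.157. Expected coverage = Φ((1.96 × 0.171 + 0.157) / 0.168) − Φ((−1.96 × 0.171 + 0.157) / 0.168) = Φ(2.93) − Φ(−1.06) ≈ 0.85, which matches the simulated 0.848. The SE describes the attenuated estimate correctly, so bias accounts for the shortfall. With no true difference in any class, rejection is 3-4%.

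**Multinomial models** (true log OR 0.60, 300 replicates). Modal estimates are 0.63 / 0.59 at gap 120 (ρ = 0). At ρ = 0.5 they are 0.57 / 0.57 at gap 90, 0.43 / 0.42 at gap 60 (coverage 80% / 83%) and 0.33 / 0.33 at gap 45 (coverage 68% / 72%).

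**Effect of correction** (ANOVA, gap 60, ρ = 0.5). BCH medians are 0.47 / 0.49, with sampling SD about 0.21 / 0.24. Approximate power is Φ(0.47/0.21 − 1.96) ≈ 61% and Φ(0.49/0.24 − 1.96) ≈ 53%.

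**The case against.** The strongest defence is that the harm is conditional and may be small. At the only SD the article states, 30 min, which it calls conservative, the stable short vs 8 h contrast is essentially intact with independent errors and the others lose at most 15%. SDs of 45-60 min appear nowhere in the article. The worst case above has entropy 0.37, which the planned entropy diagnostic would be expected to flag. This stands as a limit on size. It does not remove the problem, because the article gives no entropy value at which the second stage would change.

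A reader might infer that every contrast shrinks. The calculations do not support that. The short vs 8 h contrast can be inflated, and in the gap 45, ρ = 0 setting the improving class, whose true difference is 0, drifted to +0.08 and was rejected in 10% of replicates, against 6% with true class.

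A reader might also infer that the intervals are too narrow and so produce false positives. Planned intervals are narrower than corrected ones (0.17/0.21 and 0.18/0.24, about 20-25%). But the planned SE matches the spread of the biased estimate, and when no class differs the test is not anti-conservative.

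Finally, correction buys little power. Most of the gap to 86% / 80% comes from not observing class membership, and no method restores that. This also stands: the gain is mainly in unbiased estimates and honest intervals.

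**Conclusion.** The point holds in conditional form. The planned second stage ignores classification error. To the extent that error is present, class contrasts and odds ratios are biased, usually toward zero, and coverage falls because of that bias.

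Under the assumed 8 h, 7 h, 5.75 h and declining classes, contrasts of the declining or stable short class with 7 h keep 85-95% of the truth at the plan's SD (entropy 0.76-0.89). They keep about 49-84% at assumed SDs of 45-60 min (entropy 0.37-0.69). At entropy of about 0.95 or more the harm is negligible. Class means, shares, correlations and the larger SDs are all assumptions, since the article says separation is not known. The simulations also fix the number of classes, so they omit the uncertainty from choosing it.

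It would be tempting to conclude that the study's main result is undermined. The documents do not support that: the primary hypothesis, that distinct trajectories exist, does not use the assigned label. The secondary and supplemental hypotheses do. This should be fixed; it is not a fatal defect.

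**What to change.** In the Data analysis section:

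- Make a bias-adjusted three-step analysis (BCH weights, or ML with the estimated classification-error matrix) the main analysis for the weight, body fat, calorie and activity outcomes.
- Use the ML three-step multinomial model for predictors of class membership.
- Report relative entropy and the classification table.
- Show the modal-assignment results alongside as a sensitivity analysis.
- State in advance that the ML three-step or a one-step joint model is used if poor separation makes BCH unstable, so that the choice is not made after the results are seen.

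The cost is a change of wording and modest programming; design, sample size and data collection are unaffected. Intervals become somewhat wider and the power gain is only modest. If separation proves excellent, the two sets of results will barely differ.

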### Sample size justification

The examination of sleep trajectories is a relatively novel approach and the power to detect differences among trajectory types is dependent on multiple factors [50]. Therefore, sample size is difficult to estimate prospectively with certainty for two reasons, 1) the size and separation of sleep trajectory types in our proposed sample is relatively unknown and 2) the size and separation of trajectory types is one of the most important factors for determining the power necessary to detect trajectory types. However, with a sample size of *N* = 200, trajectories with a medium and high level of heterogeneity (i.e, among slopes and/or intercepts) can be reliably detected; power > 80% and power > 95% [51]. Further, a brief simulation was conducted based on published sleep quality trajectories (albeit in a sample with different demographic characteristics) [52] and sleep quantity characteristics of young adults [i.e., setting a conservative with-in group standard deviation to 30 min [53];. With an estimated sample size of *N* = 300 (accounting for 20% attrition, *n* = 240) the model was able to recover the four sleep trajectories of previous research with a small level of variability.

